## Abstract

**Background:**

In recent years, global cholecyst-related disorders have been increasing daily. Laparoscopic cholecystectomy (LC) is an advanced gallbladder surgical technique. However, pneumoperitoneum and various factors leading to abdominal distension and other gastrointestinal dysfunctions are common postoperative complications. Although postoperative gastrointestinal dysfunction can be treated with Avimopan, this medication also has adverse reactions such as nausea and vomiting. Acupuncture is one of the distinct treatment methods in TCM (Traditional Chinese Medicine), characterized by its simplicity, practicability, and minimal side effects. Previous studies have confirmed the effectiveness of acupuncture intervention for gastrointestinal functionality.

**Method:**

This study is a randomized, single-blind, controlled pilot clinical trial. We divided the patients into two groups: Electroacupuncture (EA) meridian acupoint group and EA non-meridian non-acupoint group. During the study period, both groups will receive routine care and education with an anticipated total of 36 individuals in each group. Both groups of patients will be treated with electroacupuncture (EA) after surgery, and in the morning of the day following the operation, with each session lasting 30 min. Specifically, the EA meridian acupoint group had intervention at the bilateral Zusanli (ST36) and Neiguan (PC6) points, while the EA non-meridian non-acupoints group had selected acupoint interventions at about 1.5 cm from ST36 and PC6. We will use the VAS (Visual Analogue Scale) and abdominal distension grading to evaluate the degree of patients’ postoperative abdominal distension 1–6 h and 24 h after surgery to obtain outcome assessments.

**Expected outcome:**

This study aims to scientifically and standardly evaluate the impact of EA in lessening post-LC abdominal distension through a clinical trial. We hope to get direct clinical evidence to demonstrate the role that EA can play in the ERAS (enhanced recovery after surgery) in patients post-LC. We hypothesise that the therapeutic effect of EA at meridian acupoints is superior to EA at non-meridian non-acupoint in the comprehensive intervention after LC.

**Clinical Trial Registration:**

http://www.chictr.org.cn, identifier ChiCTR2300073134.

## Background

1

Gallbladder-related diseases are increasing worldwide in recent years (1). In the context of the high prevalence of gallbladder diseases, the application of laparoscopic cholecystectomy (LC) has significantly increased. LC is an advanced surgical technique for gallbladder removal that utilizes laparoscopic technology to perform the surgery through small abdominal incisions. It offers advantages such as minimal invasiveness, low complications, and fast postoperative recovery compared to traditional open surgery (2). Therefore, LC has become the preferred treatment option for common biliary diseases (3). During the LC procedure, the surgeon creates small incisions in the patient's abdominal wall and inserts laparoscopic instruments into the abdominal cavity to perform the surgery. The gallbladder and surrounding organs are visualized using a microscopic camera, and then the gallbladder is removed using the instruments. This surgical approach is mainly suitable for patients with gallstones, cholecystitis, and other related conditions, with a typical surgery duration of 1–2 h. Patients can quickly resume normal diet and activities postoperatively (4), although mild to moderate pain may be present. However, serious complications of LC may include damage to the common bile duct or other bile ducts (4), highlighting the significance of considering the potential complications associated with LC (5).

During the LC procedure, nitrogen or carbon dioxide is injected into the abdominal cavity for visualization of the internal organs (6). These gases need to be expelled from the body after the surgery, but sometimes they may remain in the abdominal cavity. As a result, abdominal distension and other gastrointestinal dysfunctions caused by pneumoperitoneum and various factors are common complications after LC (7, 8). According to an early study (9), 80% of patients with gallstones who underwent cholecystectomy experienced severe digestive disorders, suggesting that gallbladder inflammation may be a contributing factor to gastric bloating-related digestive disorders. Additionally, due to pneumoperitoneum, surgical trauma, and the effects of anesthesia, normal bowel movements often fail to recover within 24 h after the surgery. Furthermore, severe abdominal distension may impede venous blood flow in the inferior vena cava, leading to complications such as deep vein thrombosis (10). Therefore, improving abdominal distension, pain, and other gastrointestinal dysfunction after LC surgery plays an important role in promoting patient recovery and improving postoperative quality of life.

Postoperative gastrointestinal dysfunction can be treated with alvimopan, but this medication also has adverse effects such as nausea and vomiting (11), which makes it difficult to guarantee patient benefits. Acupuncture, a treatment used in Traditional Chinese Medicine (TCM) for centuries, is believed to have certain effectiveness in improving gastrointestinal function (12). For example, acupuncture is thought to treat irritable bowel syndrome through mechanisms such as gastrointestinal motility, visceral hypersensitivity, the immune system, neurotransmitters, and the brain-gut axis (13). Studies and our previous review have shown that acupuncture has gained attention as an effective method for treating postoperative gastrointestinal symptoms and intestinal motility disorders (14–17). Electroacupuncture (EA) after laparoscopic cholecystectomy (LC) significantly promotes postoperative intestinal function recovery in patients (18). It is currently unclear whether EA after LC can help improve gastrointestinal symptoms such as bloating. Furthermore, we aim to confirm the effectiveness of commonly used acupoints in restoring gastrointestinal function. Therefore, this study aims to evaluate the efficacy of EA in reducing postoperative bloating and promoting gastrointestinal recovery time after LC. We hypothesize that EA can further accelerate the recovery of intestinal function after LC.

## Methods/design

2

### Design

2.1

This study is a single-center, randomized controlled clinical trial. The study aims to evaluate the clinical efficacy and efficiency of EA in treating post-laparoscopic cholecystectomy bloating. This study is designed as a superiority trial, hypothesizing that the efficacy of EA at meridian acupoints is superior to sham EA in the integrative medical care after laparoscopic cholecystectomy. The protocol of this clinical trail is based on or refers to the following standard items: the Standard Protocol Items: Recommendations for Interventional Trials (SPIRIT) checklist (19) and its TCM extension (20); Consolidated Standards of Reporting Trials (CONSORT) (21); Standards for Reporting Interventions in Clinical Trials of Acupuncture (STRICTA) (22); WHO standard acupuncture point locations in the Western Pacific region. This clinical trial protocol is approved by the Ethics Committee of Putuo District Central Hospital, Shanghai (approval number: PTEC-A-2023-29-1) and registered with the Chinese Clinical Trial Registry (Registration number: ChiCTR2300073134).

### Patient recruitment

2.2

This study is expected to include patients who undergo LC at the Department of General Surgery, Putuo Hospital, Shanghai University of Traditional Chinese Medicine, from July 1, 2023 to December 31, 2024. Patients who express interest will be recruited through preoperative interviews and pre-screening. After confirmation by clinical physicians and signing an informed consent form, baseline data will be collected. The criteria for pre-screening were defined as Patients with benign gallbladder diseases requiring LC as outlined in the “Expert Consensus on Surgical Treatment of Benign Gallbladder Diseases in China (2021)” (23) (Figure 1).

**Figure 1 F1:**
[figure not shown]
Flow chart.

### Patient selection criteria

2.3

#### Inclusive criteria

2.3.1

1. Aged 18–70, both males and females will be included;2. Diagnosed with benign gallbladder disease, in accordance with the indications for laparoscopic cholecystectomy as outlined in “Routine Laparoscopic Cholecystectomy” (24), requiring LC resection;3. Signed informed consent form;4. Possessing a physical status of American Society of Anesthesiologists (ASA) classification III or better, including the following three grades: Grade I: Healthy, well-nourished, and with normal organ function; Grade II: Mild systemic disease, with adequate compensatory mechanisms; Grade III: Severe systemic disease that limits activity but is not incapacitating;5. Undergoing abdominal surgery for the first time. Voluntarily participating in this clinical study.

Only those who meet all the above criteria can be included.

#### Exclusion criteria

2.3.2

1. Patients requiring simultaneous combined procedures;2. Patients experiencing severe intraoperative or postoperative complications requiring intensive care;3. Patients using medications affecting the intestines (e.g., Chinese herbal medicine) within one month;4. Patients who have undergone acupuncture treatment within six months;5. Patients with cardiac pacemakers;6. Patients currently participating in other clinical studies within six months;7. Patients with a history of syncope, epilepsy, or psychiatric disorders;8. Patients undergoing epidural anesthesia;

Meeting any of the above criteria will result in exclusion.

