#### Eliminate and detachment criteria

2.3.3

Patients meeting the following criteria during the study will be eliminated:
1.Those found to not meet the above diagnosis and inclusion criteria after randomization;2.Patients were converted to open surgery intraoperatively or diagnosed with other disorders intraoperatively and postoperatively.3.Patients with poor compliance who fail to receive acupuncture treatment as prescribed;4.Patients experiencing severe adverse reactions, complications, and special physiological changes that make it inappropriate to continue the trial.Subjects meeting the following criteria during the study will be considered as dropouts:
1.Those found to not meet the inclusion criteria or meet any of the exclusion criteria after randomization;2.Patients requesting to withdraw from the study;3.Patients experiencing intolerable adverse events/serious adverse events, where the investigator judges that the risk of continuing participation in the trial outweighs the benefits;4.Patients who lost to follow-up.

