##### Procedure

2.5.2.3

All patients are placed in a supine position and the acupoints are routinely disinfected. The 40 mm disposable sterile acupuncture needle (Hwato, Suzhou, China) was used. The needle was directly punctured 0.5∼1 cun (about 15–30 mm). The acupuncture manipulation is reinforcing and reducing to DeQi. The patient may not be fully awakened at the time of the first acupuncture, so we defined DeQi as the sensation of blockage felt by the acupuncturist during the maneuver. After, use an electric wire to connect both sides of ST36, using a continuous wave type with a frequency of 2 Hz and an intensity of 2–3 mA. There were two times of EA interventions, with the first intervention starting after the surgery, and the second intervention lasting 30 min on the morning of the second postoperative day. When taking the needle, gently press with your hand and use a clean cotton pad to prevent bleeding.

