#### Secondary outcomes

2.6.2

Secondary outcomes include the time for postoperative abdominal distension to disappear, length of hospital stay, postoperative pain, nausea and vomiting, time to first independent walking, time to first postoperative flatus, time to first postoperative defecation, postoperative complications, and other qualitative indicators for patients.
1.Time for postoperative abdominal distension to disappear: Refers to the difference between the time for postoperative abdominal distension to disappear and the end of the surgery. Patients and their family members should be carefully informed to observe and report the time when the postoperative abdominal distension sensation disappears, and the details should be recorded in the Case Report Form (CRF).2.Postoperative pain, nausea, and vomiting: Postoperative pain and nausea will be assessed using the Visual Analog Scale (VAS). The degree of pain and nausea will be observed and recorded every hour from 1 to 6 h postoperatively and at 24 h, and the frequency of vomiting will be recorded.3.Time to first postoperative flatus: Refers to the difference between the time of the first postoperative flatus and the end of the surgery. Patients and their family members should be carefully informed to observe and report the time of the first postoperative flatus, and the details should be recorded in the CRF.4.Time to first postoperative defecation: Refers to the difference between the time of the first postoperative defecation and the end of the surgery. Patients and their family members should be carefully informed to observe and report the time of the first postoperative defecation, and the details should be recorded in the CRF.5.Length of hospital stay: The time from the end of the surgery to discharge.6.Postoperative complications: Other postoperative complications will be recorded in the CRF.7.Other qualitative indicators for patients.

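### Exclusion criterion 2 has no time limit, so a severe postoperative complication after the first session is both a ground for exclusion and an outcome, in conflict with the stated analysis set

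*Protocol article*

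**What the plan says.** All references are to the protocol article.

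- **Entry (section 2.2).** Enrolment takes place before surgery: "Patients who express interest will be recruited through preoperative interviews and pre-screening". Then: "After confirmation by clinical physicians and signing an informed consent form, baseline data will be collected".
- **Exclusion (section 2.3.2).** Criterion 2 is "Patients experiencing severe intraoperative or postoperative complications requiring intensive care". The list closes with "Meeting any of the above criteria will result in exclusion". No time limit is attached to either sentence.
- **After randomization (section 2.3.3).** Dropout item 1 covers "Those found to not meet the inclusion criteria or meet any of the exclusion criteria after randomization". Elimination item 2 covers "Patients were converted to open surgery intraoperatively or diagnosed with other disorders intraoperatively and postoperatively". Elimination item 4 covers severe reactions or complications that make continuing unsuitable.
- **Treatment (section 2.5.2.3).** There are two sessions, "with the first intervention starting after the surgery". The section allows that the patient may not yet be fully awake at that session.
- **Outcomes (sections 2.6.2 and 2.6.3).** Secondary outcome 6 reads "Postoperative complications: Other postoperative complications will be recorded in the CRF". Adverse events are monitored during the study, and serious ones go to the Ethics Committee within 24 h.
- **Analysis (section 2.8).** The set called intention-to-treat consists of patients with at least one session. A per-protocol set serves as a robustness check. Missing data are handled by last observation carried forward and multiple imputation.

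**The concern.** An entry criterion should be decidable before a patient is allocated. The postoperative part of criterion 2 is not decidable at preoperative enrolment. Because the first session comes so soon after surgery, much of the period in which a postoperative complication can occur lies after treatment has begun. Dropout item 1 then carries the exclusion list past randomization, so criterion 2 works as a removal rule that depends on an event after treatment.

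That event is also something the trial sets out to count. If patients who have it are removed, the complication rate is understated in whichever arm they came from. Their data on hospital stay, flatus and defecation, probably among the less favourable, may go with them. Randomization no longer protects a comparison restricted in this way. Section 2.7 says the results will feed the sample size of a later trial, so distorted attrition and complication figures would carry forward.

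**Working it through.** **1. The plan's own sample size.** Section 2.7 gives 30 patients, 20% dropout and 72 in total; the abstract gives 36 per group. Reading the 30 as per arm, 30 × 1.2 = 36 and 2 × 36 = 72, which reproduces the stated figure. There is no power calculation to reproduce, and the present point does not depend on one.

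**2. One patient followed through the text.** Take a patient who consents before surgery, is allocated, receives the first session, and then has a severe complication that needs intensive care.

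| Section | What happens to this patient |
|---|---|
| 2.3.2, criterion 2 | Excluded |
| 2.3.3, dropout item 1 | Dropout, because an exclusion criterion is met after randomization |
| 2.3.3, elimination item 4 | Eliminated, if continuing is judged unsuitable |
| 2.3.3, elimination item 2 | Eliminated, if the event counts as another disorder diagnosed postoperatively |
| 2.6.2, item 6 | Counted as an outcome |
| 2.6.3 | Recorded as an adverse event, and reported if serious |
| 2.8 | Kept in the main analysis, having had one session |

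Sections 2.3.2 and 2.3.3 point towards removal; sections 2.6.2, 2.6.3 and 2.8 point towards counting. No sentence ranks them.

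The overlap is confined to the postoperative half of criterion 2. Intraoperative complications are not a listed outcome.

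**3. Size per patient.** One patient in an arm of 36 is 1/36 = 2.8 percentage points. If the patient leaves both numerator and denominator, a count of k complications goes from k/36 to (k − 1)/35:

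- k = 1: 1/36 = 2.8% becomes 0/35 = 0%
- k = 2: 2/36 = 5.6% becomes 1/35 = 2.9%
- k = 3: 3/36 = 8.3% becomes 2/35 = 5.7%

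The shift is therefore between 2.6 and 2.8 points for each removed patient at these counts.

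**4. How many patients.** The documents give no rate of complications requiring intensive care. The rates p below are assumptions for illustration. The expected number is 72p, and the chance of at least one is 1 − (1 − p)^72.

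| Assumed rate p | Expected among 72 | Chance of at least one |
|---|---|---|
| 0.5% | 0.4 | 30% |
| 1% | 0.7 | 52% |
| 2% | 1.4 | 77% |
| 5% | 3.6 | 98% |

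Only events after allocation raise the present problem, so if p also includes intraoperative events the relevant numbers are lower.

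**The case against.** The strongest reply is that section 2.8 already settles the matter. A patient with a complication after session one is a dropout under section 2.3.3, has had one session, and so stays in the main set with missing values imputed. Section 2.6.3 monitors adverse events with no exemption for excluded patients. On that reading nobody leaves the comparison, and the words on postoperative events in criterion 2 are merely loose drafting. This stands in part: it shows that loss from the comparison is not certain. It does not remove the conflict, because section 2.3.2 says that meeting a criterion results in exclusion, section 2.3.3 has separate lists for dropouts and eliminated patients, and nothing says that section 2.8 overrides them.

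It is also fair to say that the numbers are small, that complications are one of several secondary outcomes, and that the trial calls itself a pilot. All of that stands and limits the weight of the point.

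A reader might also infer from the elimination rule for conversion to open surgery that envelopes are opened before the operation, and so are spent on patients who never become eligible. The article does not support this. Section 2.4 gives no time for opening envelopes, the flow chart is not shown, and a consented patient can be in the study without being randomized. Allocation after surgery would make the intraoperative half of criterion 2 a valid screen. Even with earlier allocation, losses before any treatment would be unrelated to treatment received.

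**Conclusion.** The point holds for the postoperative half of criterion 2. As written, the entry rule depends on an event that can follow treatment, that event is also a secondary and a safety outcome, and sections 2.3.2 and 2.3.3 conflict with section 2.8 on whether the patient is analysed. If the removal rules are followed, each affected patient costs about 2.8 percentage points of a 36-patient arm, and these are the most severe cases. The expected number is unknown from the documents and probably small.

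Two stronger readings should not be drawn. First, safety information is not shown to be lost, since reporting of serious adverse events still applies. Second, unequal removal between arms is possible but not shown: section 4 says the acupuncturists are not blinded, but section 2.4 gives observation and analysis to separate people.

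The conclusion rests on reading criterion 2 without an unstated time limit and dropout item 1 as applying to it. Both follow the text as it stands. It does not depend on when envelopes are opened, provided that some postoperative complications occur after the first session.

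**What to change.** 1. **Section 2.3.2:** limit criterion 2 to events known before allocation.
2. **Sections 2.6.2 and 2.6.3:** state that any complication after allocation is counted as secondary outcome 6 and as an adverse event, and is not a ground for exclusion from the analysis.
3. **Sections 2.3.3 and 2.8:** reconcile elimination items 2 and 4 and dropout item 1 with this. Separate ending treatment or participation from leaving the analysis, and say which section decides the analysis set.

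Rules on stopping treatment for safety stay as they are; the change concerns who is counted.

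As a clarification only, section 2.4 could state when the envelope is opened. If it is after surgery, once intraoperative eligibility has been confirmed, saying so would make the intraoperative half of criterion 2 plainly a pre-allocation check. The envelope holder would then have to be reachable at that time.

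The cost is a short text amendment. Consent and baseline assessment stay before surgery, and the sample size is unchanged.

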#### Eliminate and detachment criteria

2.3.3

Patients meeting the following criteria during the study will be eliminated:
1.Those found to not meet the above diagnosis and inclusion criteria after randomization;2.Patients were converted to open surgery intraoperatively or diagnosed with other disorders intraoperatively and postoperatively.3.Patients with poor compliance who fail to receive acupuncture treatment as prescribed;4.Patients experiencing severe adverse reactions, complications, and special physiological changes that make it inappropriate to continue the trial.Subjects meeting the following criteria during the study will be considered as dropouts:
1.Those found to not meet the inclusion criteria or meet any of the exclusion criteria after randomization;2.Patients requesting to withdraw from the study;3.Patients experiencing intolerable adverse events/serious adverse events, where the investigator judges that the risk of continuing participation in the trial outweighs the benefits;4.Patients who lost to follow-up.

### Randomization, blinding, and grouping

2.4

The experiment was grouped using SPSS 26.0 (IBM, USA). A random number table was generated, with “0” representing the “EA group” and “1” representing the “EA-sham group.” The grouping results will be written on paper, placed in sealed and opaque envelopes, and kept by a dedicated person. A researcher who did not know the grouping results opened the envelopes in sequence according to the envelope numbers and assigned patients to the corresponding treatment groups, with no one allowed to make unauthorized changes. The study strictly adhered to the three-separation principle of blinding, which means that observation recording, treatment operations, and data analysis were conducted separately. Random grouping was the responsibility of a dedicated person, observation recording was completed by non-operators, treatment operations were carried out according to the envelope grouping, and data statistics and analysis were the responsibility of a dedicated person to ensure the authenticity of clinical records. Patients in both EA groups were unaware of their treatment group.

